#### Mental health

The prevalence of anxiety and depression in CRC patients is 13–57% [44], and one of the important factors is the adverse effects of chemotherapy [45]. Hospital Anxiety and Depression Scale (HADS), an effective questionnaire with 14 items, will be used to assess depression and anxiety in each chemotherapy cycle. Each item is on a 4-point scale and final scores are proportional to the degree of anxiety and depression.

#### Data analysis

The visiting time of the participants is in accordance with the treatment course, so as to facilitate the retention of the participants. The measured data for each visit will be collected on paper and then recorded electronically on a secure, locked office computer. The paper version of the data will be locked in a bookcase. Only the investigators running in the study will have access to the final study dataset.

The obtained data will be analyzed by the SPSS software V26.0 (IBM, USA). Continuous data will be expressed as mean ± standard deviation (SD), and categorical data will be expressed as the number of cases (*n*) and percentage (%). Differences in parameter continuous variables and asymmetric variables between groups will be analyzed through independent samples *t* test and Mann-Whitney *U* test, respectively, using a paired *t* test to assess the effect of the intervention in each group. The normality of data will be assessed using the Kolmogorov-Smirnov test.

The results will be regarded as statistically significant if *p* values< 0.05.

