#### Randomization and blinding

After signing the informed consent form and complete baseline questionnaires, patients with LSCRC (*n* = 50) and RSCC (*n* = 50) will be randomly divided into prebiotic group (*n* = 25) and control group (*n* = 25) in a 1:1 allocation ratio, respectively. The random number will be generated by a computer and sealed in envelopes by an investigator who will not be involved in running the study and placed in a safe place. Before data analysis, participants and investigators will not know the contents of the bags, allocation, and study treatments.

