#### Sample size calculation

Since there is no clinical trial assessing the effect of intestinal flora on the bioavailability of chemotherapy drugs and the intervention endpoints of intestinal flora are currently unable to determine, the sample size is estimated based on the data from a previous clinical trial [22] which assessed the effects of synbiotics intervention on chemotherapy-related adverse effects (including diarrhea, appetite loss, nausea, and vomiting) for CRC patients received post-operative chemotherapy, showing that 20 volunteers per group had 90% power at an alpha level of 0.05 to detect significant differences. Combined with the above data from the clinical trial, the sample size in this study will be calculated statistically by the Power Analysis and Sample Size Software (PASS). Considering the long duration of the study (3 months) and the expected withdrawal of participants during the intervention, we plan to recruit *n* = 25 participants per group (*n* = 100 total).

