#### Data collection and sample handling

The overall study design is depicted in Fig. 1. Assessment of participants will be conducted at the perioperative (baseline = week 0), pre-treatment (week 3), post-treatment (week 15), and in each chemotherapy cycle. The primary outcomes will be the differences in the microbiota composition at different CRC tumor sites and differences in gut microbiota composition, adverse reactions, and blood concentration of capecitabine in patients with CRC treated for 12 weeks with XOS or placebo. The secondary outcomes will include blood indicators (hepatic and renal function, blood glucose, blood lipid, and inflammatory cytokines), SCFAs concentration, QoL, and mental health.

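### The article words the XOS comparison as pooled but sizes it by tumour location, and its analysis section does not say whether the pooled, left-sided or right-sided test decides

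*Protocol article*

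**What the plan says.** Some parts of the article describe one pooled comparison. Data collection and sample handling defines the primary XOS outcomes, including "blood concentration of capecitabine in patients with CRC treated for 12 weeks with XOS or placebo", for CRC patients as a whole. The Objectives likewise state the XOS aims (bioavailability, adverse effects, quality of life) for CRC patients without splitting by location.

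Other parts work by location:
- The Abstract (Methods) and Randomization and blinding divide 50 left-sided and 50 right-sided patients "in a 1:1 allocation ratio, respectively", giving 25 v 25 in each location.
- Sample size calculation takes from an earlier synbiotic trial that "20 volunteers per group had 90% power at an alpha level of 0.05 to detect significant differences", and then says "we plan to recruit *n* = 25 participants per group (*n* = 100 total". Since 4 × 25 = 100, a group here is one location-by-arm cell.
- The Abstract (Background) and the end of the Introduction present the effect of XOS at different tumour locations as something the trial studies.

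Interventions uses the word in a third way, giving 25 per group for prebiotic and 50 per group for control.

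Data analysis then reads "Differences in parameter continuous variables and asymmetric variables between groups will be analyzed through independent samples" *t* test and Mann-Whitney *U* test, followed by "The results will be regarded as statistically significant if" p is below 0.05. It does not define the groups. It names no location term, interaction test, order of testing or division of alpha.

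**The concern.** A two-sample test needs two groups, and this design has four cells. For one outcome, such as capecitabine concentration, an analyst following the text could test XOS against placebo in all patients, in the left-sided patients or in the right-sided patients. Each test would be held to p<0.05, with no rule on which one answers the question. This arises within a single endpoint and would remain if the number of primary outcomes were cut.

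Two things are at stake. First, if any of the three tests may count as success, the error rate for that outcome exceeds the stated 5%. Second, when XOS works equally well on both sides, small cells will often give one significant and one non-significant location. Nothing in Data analysis stops that pattern being reported as a location-specific effect.

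**Working it through.** **Inputs from the article.** Alpha 0.05; 20 per group for 90% power; 25 recruited per cell, 100 in total; 1:1 allocation within location.

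**Assumptions.** Two-sided tests; 20 completers per cell (20/25 = 80%, so 20% withdrawal, a rate the article does not state); a *t* test on a continuous outcome; the standardised effects d used below.

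**1. The plan's own figure.** No effect size, SD or event rate is given, so n = 20 cannot be reproduced, only solved backwards:

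d = (z₀.₉₇₅ + z₀.₉₀) × √(2/n) = (1.960 + 1.282) × √(2/20) = 1.03

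The noncentral *t* gives 1.05. For 40 v 40 the same formula gives 3.242 × √(2/40) = 0.73. So 20 per group means different things under the two readings. By location, it describes power of 90% at d ≈ 1.03. Pooled, the trial would have 40 v 40 completers and 90% power at d ≈ 0.73.

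**2. No true effect.**
- Either location significant: 1 − 0.95² = 0.0975; 9.7% by simulation.
- Pooled, left or right significant: with z_pooled = (z_L + z_R)/√2, whose correlation with each location is 0.71, 4 million simulated draws give 11.5%.
- One named test: 5.0%.

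**3. The same true effect in both locations.** With power p in each location (20 v 20), P(exactly one significant) = 2p(1 − p) and P(both) = p². From the noncentral *t*:

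| d | p per location | exactly one | both | pooled 40 v 40 |
|---|---|---|---|---|
| 1.05 | 90.0% | 18% | 81% | 99.6% |
| 0.8 | 69.3% | 43% | 48% | 94.2% |
| 0.5 | 33.8% | 45% | 11% | 59.8% |

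Between the last two rows the chance of disagreement passes through its maximum of 2 × 0.5 × 0.5 = 50%, where p = 50%.

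**4. An effect in one location only (d = 1.025 and 0).** The average effect is 1.025/2 = 0.5125. Pooled power is Φ(0.5125 × √(40/2) − 1.960) = Φ(2.292 − 1.960) = 63%, against 90% in the location where XOS works.

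**5. The interaction.** With 20 per cell, the difference between the two location effects has standard error √(4/20) = 0.447 in SD units. For a true difference of 1.025, power is Φ(1.025/0.447 − 1.960) = 63%. Power of 90% needs a difference of 3.242 × 0.447 = 1.45.

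**The case against.** The strongest reply is that this is mainly an omission. The full protocol and analysis plan are not shown, and a journal article may leave the deciding contrast to them. Randomising within location is ordinary stratification and fits a pooled analysis. Sizing by cell does not say that cells will be tested separately, and no section states a by-location test. On this view the natural reading is XOS versus placebo pooled, with left versus right kept for the microbiota.

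Much of this stands. A reader might infer that the article plans a separate XOS test in each location, but neither Randomization and blinding nor Sample size calculation says so. A reader might also infer that a one-sided XOS result is what the article means by personalised treatment. It does not say that: the Abstract (Discussion) and the end of the main Discussion tie that prospect to differences in tumour and gut microbiota between locations. Nor does the article say that a win in any contrast counts, so 9.7% and 11.5% describe what the wording permits and do not predict what the sponsor will do. The effect sizes are not in the article, and *t*-test power may not describe graded adverse effects.

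The reply does not remove the conflict in the text itself. The comparison is worded as pooled, sized per cell and motivated by location, the word group carries several meanings, and Data analysis relies on that word with unstratified two-sample tests.

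**Conclusion.** The point holds as an ambiguity in the article's own wording, not as proof of a planned multiple-testing strategy. One primary XOS outcome can be tested in three ways at p<0.05, with no rule on which decides.

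Its size is conditional. The false-positive rate per outcome is about 11.5% if any of the three may win and 9.7% if either location may win, against 5% for one named test. With equal true effects on both sides, exactly one location is significant in 18%, 43% and 45% of trials at d = 1.05, 0.8 and 0.5. These figures assume two-sided *t* tests, 20 completers per cell and those effect sizes. It should be corrected.

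**What to change.** - In Data collection and sample handling and in Data analysis, state that the deciding contrast for each primary XOS outcome is XOS versus placebo in all randomised patients, adjusted for or stratified by tumour location as randomised. This follows the existing wording of the primary outcomes.
- Address the location question raised in the Abstract and Introduction with a prespecified treatment-by-location interaction as a secondary analysis. Report left- and right-sided estimates with confidence intervals, and make no location-specific claim from one location's p value alone. Given its limited power, a non-significant interaction should not be read as equal effects.
- In Sample size calculation, say which contrast the 20-per-group figure refers to.
- In Interventions, reconcile the 25 and 50 per group with the four cells of 25.

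No extra patients or data are needed. The change goes slightly beyond wording, because the unstratified tests now named would give way to a stratified or adjusted analysis. It should be settled before the allocation is opened for analysis. The price is power if XOS works in one location only (about 63% pooled against 90% in that location at d ≈ 1.03), and a lone p<0.05 in one location is no longer a primary finding. If location-specific claims are the real aim, prespecifying both location tests with alpha divided between them would also remove the ambiguity.

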At present, cytotoxic drugs are generally applied for postoperative adjuvant therapy or advanced CRC patients, usually accompanied by a series of adverse effects (such as constipation, diarrhea, nausea, and bone marrow suppression) and individual differences in drug efficacy [14, 15]. In recent years, with the rise of “pharmacomicrobiomics,” the significance of the intestinal flora in regulating the host response to chemotherapeutic drugs is increasingly recognized [16]. Intestinal flora can modulate the anti-tumor activity of chemotherapy drugs [17]. The killing effectiveness of 5-Fu on CRC can be enhanced by bacterial-derived urolithin A [18]. Importantly, proteobacteria can promote the deglycosylation of capecitabine [19]. Moreover, some studies have reported that probiotics/prebiotics can reduce the adverse effects of chemotherapy. *Lactobacillus casei* variety *rhamnosus* plays a preventive role in FOLFOX-related intestinal mucositis in CRC-bearing mice [20]. In CRC patients, *L. rhamnosus* GG consumption reduced the incidence of 5-FU-induced severe diarrhea and abdominal discomfort compared with guar gum fiber [21]. Lu et al. found that synbiotics (containing a variety of probiotics and prebiotic ingredients) can help relieve postoperative chemotherapy-related adverse effects, further improving the quality of life (QoL) in CRC patients [22]. Furthermore, accumulating evidence demonstrated that prebiotics, such as non-digestible oligosaccharides, can reverse chemotherapy-induced intestinal dysbiosis through selective colonization of the probiotic bacteria [23]. In Peng’s trials, compared to those who received enteral nutrition therapy alone, surgical patients supplied with prebiotics experienced shorter durations of hospital stay and had reduced levels of inflammatory cytokines [24]. Hence, targeting the gut microbiota in clinical practice to modulate the efficacy and toxicity of chemotherapeutic drugs has a promising future.

Although there have been some reports on the effects of microecologics on modulating intestinal flora and reducing adverse effects in patients with CRC during chemotherapy, they are still very limited. Through our current knowledge, using microecologics to interfere with the bioavailability of chemotherapeutic agents in a microbiota-dependent manner has not been reported, as well as differences in the intervention effect of prebiotics on the intestinal flora of CRC patients at different primary tumor locations.

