## Objectives

Firstly, this study aims to explore the difference of tumor microbiota and the different gut microbiota changes during treatment between LSCRC and RSCC. Moreover, another goal of the trial is to investigate the effect of XOS on (i) increasing the bioavailability of cytotoxic drug, (ii) reducing the adverse effects of chemotherapy, and (iii) improving the QoL of CRC patients by modifying gut microbiota.

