### Information questionnaires and physical evaluation

The personal information of the subjects will be conducted through basic information questionnaires, including body mass index, age, gender, and dietary habit. And these data were obtained in the form of an interview. Meanwhile, physical examination (height, weight, blood pressure, heart rate, etc.) is performed before the allocation.

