A sequence similarity threshold of 97% will be used to select operational taxonomic units (OTUs) and then perform taxonomy assignments via the Usearch platform (version 7.1 http://drive5.com/uparse/). Principal coordinates analysis (PCoA) on weighted UniFrac distances will be measured on all OTUs by QIIME. Alpha diversity will be calculated through the Shannon index, Simpson index, and Chao1 metrics using mothur (version v.1.30.1 http://www.mothur.org/wiki/Schloss_SOP#Alpha_diversity). Linear discriminant analysis (LDA) will be performed on the analysis software LEfSe (http://huttenhower.sph.harvard.edu/galaxy/). Subsequently, the communities or species that have significant differences in the sample division will be selected.

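### Left-versus-right and XOS-by-location questions are paired with stated analyses that neither adjust for collected covariates nor compare the XOS effect between sites

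*Protocol article*

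**What the plan says.** The Objectives section of the protocol article opens with the aim to "explore the difference of tumor microbiota and the different gut microbiota changes during treatment between LSCRC and RSCC". Data collection and sample handling makes the site comparison a primary outcome: "The primary outcomes will be the differences in the microbiota composition at different CRC tumor sites" comes first in that list, ahead of the XOS-versus-placebo outcomes. The Introduction names as not yet reported the "differences in the intervention effect of prebiotics on the intestinal flora of CRC patients at different primary tumor locations".

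Patients "will be randomly divided into prebiotic group (*n* = 25) and control group (*n* = 25) in a 1:1 allocation ratio, respectively", separately among left-sided and right-sided cases. Only XOS or placebo is randomised; location is a stratum.

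The Data analysis section states the inferential methods: "Differences in parameter continuous variables and asymmetric variables between groups will be analyzed through independent samples *t* test and Mann-Whitney *U* test", "using a paired *t* test to assess the effect of the intervention in each group", and significance at p < 0.05. For the microbiota, the Gut microbial composition section adds principal coordinates on weighted UniFrac distances and alpha diversity indices, and "Linear discriminant analysis (LDA) will be performed on the analysis software LEfSe". None of these is stated with a covariate or an interaction term.

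Baseline information is taken through "basic information questionnaires, including body mass index, age, gender, and dietary habit". Food guidance and records adds a 72-hour food record with each stool sample, and treats diet as something that interferes with the microbiota.

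**The concern.** Two of the trial's questions are paired with methods that do not answer them.

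1. **Left versus right.** Patients are not assigned to a tumour location, so any observed difference may partly reflect who gets tumours on which side. The Introduction itself says the sites differ in clinical characteristics. The variables needed to examine this are collected, but no stated analysis uses them.

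2. **XOS by location.** A claim that XOS acts differently on the two sides needs a direct comparison of the two effects. The stated tests compare two groups, or look at change within one group. With four groups of 25, they lend themselves to a pattern of significance on one side but not the other, which is not evidence that the effects differ.

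The Discussion hopes that the site data may inform treatment strategies based on tumour location. That hope rests on these contrasts.

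**Working it through.** **Inputs from the article.** 20 per group for 90% power at alpha 0.05; 25 per group recruited (100 in total); allocation 1:1 within each location. **Assumed:** two-sided tests, a continuous outcome, and the effect sizes below. The article gives no effect size, SD or event rate.

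**The plan's own figure.** The 20 per group cannot be reproduced without an effect size, so I solved for the effect it implies.
- Normal approximation: d = (1.960 + 1.282) × √(2/20) = 1.025 SD.
- Noncentral t: d = 1.05 SD.
- Going from 20 to 25 fits 20/(1 − 0.20) = 25, about 20% withdrawal.

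This sizing rests on adverse effects in an earlier synbiotic trial. It covers neither left versus right nor arm by location.

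**Separate tests by side.** Suppose XOS has exactly the same effect d on both sides and each side is tested alone with power p. The chance that exactly one side is significant is 2p(1 − p), computed here from unrounded power.

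| n per cell | d (SD) | p | 2p(1 − p) |
|---|---|---|---|
| 20 | 0.50 | 0.338 | 0.447 |
| 20 | 0.65 | 0.517 | 0.499 |
| 20 | 0.80 | 0.693 | 0.425 |
| 20 | 1.05 | 0.900 | 0.180 |
| 25 | 0.80 | 0.791 | 0.330 |

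At 20 per cell the range is therefore about 18% to 50%, with no true difference between sides.

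**Effect detectable with 90% power (noncentral t).**
- One side alone, 20 per arm: 1.05 SD.
- Both sides with location in the model, 40 per arm: about 0.73 SD. The normal approximation gives 3.242 × √(2/40) = 0.725.
- At d = 0.8, power is 0.693 in one side and 0.942 with both.

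**Arm by location.** The contrast is a difference of two differences, with variance 4 × SD²/n per cell and 4(n − 1) degrees of freedom.
- At 20 per cell it is detectable at 1.47 SD with 90% power, or 1.27 SD with 80%. The normal approximation for 90% is 3.242 × √(4/20) = 1.45.
- If XOS had the full 1.05 SD effect on one side and none on the other, power would be 64% at 20 per cell and 74% at 25.

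**Confounding of left versus right.** The article gives nothing to quantify this, so I used assumed values: 50 versus 50 patients, no true site effect, and one covariate that differs between sides by 0.2 to 0.5 SD and correlates 0.2 to 0.4 with the outcome (4,000 simulated trials per setting).
- The unadjusted t test rejects in about 5% to 17% of trials.
- Adjusting for the covariate keeps the rate at about 5%.
- Check on the upper end: the bias is 0.5 × 0.4 = 0.2 SD, so the noncentrality is 0.2/√(2/50) = 1.0, which gives 17%.
- A total bias of 0.3 SD from several covariates would give 32%.

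**The case against.** The strongest reply is that this is a condensed article, and that covariates, interaction terms and blocking usually belong in an analysis plan, which may exist and is not shown. The Data analysis paragraph is generic and does not exclude models. That limits how firmly the point can be put. It does not remove it, because the article names its tests and none of them fits these two questions.

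Several stronger readings are tempting, and the article does not support them:

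- **That two-sample tests are the whole microbiota plan.** They are not; ordination, alpha diversity and LEfSe are also planned. These too are given without covariates or an interaction.
- **That the site comparison is confounded.** No data in the article show age, sex, BMI or diet differing by side. The risk is uncontrolled, not demonstrated, and for one weak covariate it is small. It does not touch XOS versus placebo, which is randomised within each side.
- **That each treatment comparison uses only half the patients.** The 25-per-group sizing suggests by-side testing, but the primary outcome text describes XOS versus placebo in patients with CRC without a split.
- **That tumour, para-carcinoma and normal mucosa are treated as independent samples.** The article says only that all three are collected. Left versus right within one tissue type uses one value per patient.
- **That a differing XOS effect by side is a formal hypothesis.** It appears as a knowledge gap in the Introduction, not as a numbered objective, and the personalised-treatment statement is worded as a possibility.

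**Conclusion.** The point holds in a limited form. As stated, the analyses give no adjusted left-versus-right comparison, although that contrast is the first objective and a primary outcome, is not randomised, and has its main candidate confounders on record. They also give no test of whether the XOS effect differs between sides.

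The 18% to 50% figure depends on three things: the assumed effect of 0.5 to 1.05 SD, by-side testing at 20 per cell, and a reader drawing a site difference from the two p values. The gain from 1.05 to 0.73 SD also applies only if by-side testing is what is intended. The 5% to 17% false-positive range rests entirely on assumed covariate values. The absence of a stated arm-by-location comparison depends on none of these assumptions. This is a change that should be made, at little cost; it does not invalidate the randomised comparison.

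**What to change.** State the following in the analysis plan.

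1. **XOS versus placebo.** Fit one model of the type each outcome needs, on all randomised patients, with arm, location (the randomisation stratum) and the baseline value where one is measured. Make the location-adjusted arm effect the main result.
2. **Arm by location.** Add the interaction in a further model and report it with a 95% CI. Label it exploratory and state that at 20 per cell only about 1.47 SD (90% power) or 1.27 SD (80%) is detectable. Make no claim of a site difference from separate by-side p values.
3. **Left versus right.** Use regression, or PERMANOVA for community composition, adjusted for age, sex, BMI and diet. Report the result as an association; an unadjusted description can stand beside it.
4. **Tissue types.** If tumour, para-carcinoma and normal mucosa are compared with one another, treat patient as a block.

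The listed covariates are already collected, so no new data or patients are needed. The cost is wording, a few degrees of freedom and some extra analysis work.

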#### Blood tests

Venous blood samples will be collected before preoperative bowel preparation, at 3 weeks (pre-treatment) and 15 weeks (post-treatment). After fasting for 12 h, venous blood will be collected into a coagulating tube in the morning and centrifuged at 3000 rpm for 10 min for obtaining the upper serum (Thermo, USA). In addition to some of the usual blood biochemical indexes, we will use commercial enzyme-linked immunosorbent assay (ELISA) kits to assess the levels of inflammatory cytokines, including tumor necrosis factor-α (TNF-α), interleukin-1β (IL-1β), and interferon gamma (IFN-γ). Cellular immune indices, including T lymphocytes (CD3+), helper inducer T cells (CD3+CD4+), and suppressor/cytotoxic T cells (CD3+CD8+), will be measured by BD-FACS Canto II flow cytometer (Becton Dickinson, USA).

For the purpose of evaluating the bioavailability of chemotherapy drugs in participants, the blood concentration of capecitabine will be measured at 15 weeks (after intervention). On the third day of the fifth cycle of treatment (taking capecitabine for at least four meals), 5 mL venous blood samples will be collected 2 h after taking medicine in the morning, put into a tube with ethylene diamine tetraacetic acid (EDTA) anticoagulant, and sent to the pharmacy department of the hospital for testing immediately.

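### The XOS effect is assigned to paired t tests inside each group, where chemotherapy alone can cause a change, and no named test compares the effect between tumour locations

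*Protocol article*

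**What the plan says.** Data analysis names two kinds of test.

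- **Between groups:** "Differences in parameter continuous variables and asymmetric variables between groups will be analyzed through independent samples" t test, or Mann-Whitney U for asymmetric variables.
- **Within groups:** a paired t "test to assess the effect of the intervention in each group".

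The threshold is p < 0.05. Sidedness is not stated, nor whether the between-group tests compare week-15 values or changes, nor whether a group is a whole arm (50) or an arm within one location (25).

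Under Randomization and blinding, the 50 left-sided and 50 right-sided patients "will be randomly divided into prebiotic group" or control 1:1 within each location, so location is a stratum. Blood is drawn before surgery and "at 3 weeks (pre-treatment) and 15 weeks (post-treatment"), and stool follows the same schedule (Gut microbial composition). Capecitabine concentration is the exception: Blood tests gives one measurement, after the intervention. Study design places the intervention within postoperative chemotherapy for both arms.

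On location, Objectives asks about tumour microbiota and "the different gut microbiota changes during treatment between LSCRC and RSCC". The Abstract (Background) and the Introduction go further. The first aims to examine XOS in patients with tumours at different sites, and the second names a difference in the prebiotic's effect by site as something not yet reported.

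**The concern.** A paired test asks whether an arm changed between week 3 and week 15. Over those 12 weeks every patient has chemotherapy and is recovering from surgery, so the outcomes can move in both arms with no contribution from XOS. Only the contrast with placebo isolates XOS, and that contrast is what randomisation provides. A sentence that gives the intervention effect to the paired test invites two wrong readings: that a significant change under XOS is an XOS effect, and that significance under XOS but not under placebo is one.

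The same trap exists for location. None of the listed tests compares the XOS effect on the left with that on the right. Separate tests by location would leave the reader comparing two p values, although the Discussion offers the results as a possible basis for treatment strategies by tumour location.

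**Working it through.** **The plan's own figure.** Sample size calculation says "20 volunteers per group had 90% power at an alpha level of 0.05 to detect significant differences", taken from an earlier synbiotic trial, with no effect size, SD or event rate. It cannot be reproduced, only inverted: 20 per group at 90% power and two-sided 0.05 imply a difference of 1.05 SD (noncentral t; 1.03 by normal approximation). Going from 20 to 25 corresponds to 20% withdrawal, since 20 / (1 − 0.20) = 25.

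**Inputs.** From the article: 25 per location-by-arm cell, alpha 0.05. Assumed, because the article gives none: two-sided tests, the size of the common change, the correlation between week 3 and week 15, and a true effect of 0.5 SD.

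**1. Paired test with no XOS effect.** Let δ be the change common to both arms, in SDs of the paired differences. The paired t has n − 1 degrees of freedom and noncentrality δ√n. For n = 25 the noncentrality is 0.3 × 5 = 1.5, 0.5 × 5 = 2.5 and 0.8 × 5 = 4.0. With p the chance of significance in one group, exactly one of two independent groups is significant with probability 2p(1 − p).

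| δ | XOS group significant (p) | Exactly one group significant | XOS only, p(1 − p) |
|---|---|---|---|
| 0.3 | 0.30 | 0.42 | 0.21 |
| 0.5 | 0.67 | 0.44 | 0.22 |
| 0.8 | 0.97 | 0.06 | 0.03 |

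A simulation of 100,000 trials at δ = 0.5 gave 0.67 and 0.44. The between-group t test of change rejected in 0.049 of the same trials, its nominal level.

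With 20 completers per group, p is 0.25, 0.56 and 0.92, and exactly one group is significant in 0.37, 0.49 and 0.14. If the paired test is run in whole arms of 50, p is 0.55, 0.93 and 1.00, and exactly one arm is significant in 0.50, 0.12 and 0.00.

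**2. Separate tests by location.** Suppose XOS truly works by 0.5 SD in both locations. With 25 per arm the noncentrality is 0.5 × √(25/2) = 1.77, and power in each location is 0.41. Exactly one location is significant with probability 2 × 0.41 × 0.59 = 0.48.

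**3. Treatment by location.** The difference between two treatment differences has standard error SD × √(4/25) = 0.40 SD. For a true difference in effects of 0.5 SD, power is 0.24. Power of 80% needs about 1.13 SD with 25 per cell, or 1.27 SD with 20.

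**4. Week-3 adjustment.** ANCOVA multiplies the residual variance of the week-15 value by 1 − r². With 50 per arm and a true difference of 0.5 SD, power is 0.70 unadjusted.

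| Assumed r | 1 − r² | Power |
|---|---|---|
| 0.3 | 0.91 | 0.74 |
| 0.5 | 0.75 | 0.82 |
| 0.7 | 0.51 | 0.93 |

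**The case against.** The strongest reply is that the plan does contain a valid test. The between-group comparisons come first in Data analysis, the paired test follows as a subordinate clause, and Data collection and sample handling words the treatment outcomes as differences between XOS and placebo patients. That the authors will argue from significance in one arm only is a prediction; the article does not say so. This stands, and it limits the point. A reader might infer that the whole analysis is invalid, and the documents do not support that: an unadjusted t or Mann-Whitney test between randomised arms is sound and loses only precision.

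A reader might also infer that the week-3 values are thrown away. The article does not say whether the between-group tests use changes, and covariates are often left to a fuller plan. Lack of adjustment is therefore a missed gain and not an error.

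Nor can it be said that the left-right question goes unanswered. Mucosal microbiota and overall change by location can be compared with two-group tests and the ordination and LEfSe methods under Gut microbial composition. Only the XOS effect by location lacks a test.

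The paired test also reaches only some primary outcomes. Capecitabine concentration has no earlier value to pair, and graded adverse effects are not natural paired-t data. Finally, 2p(1 − p) cannot exceed 0.50 and falls to 0.06 at 0.8 SD, so disagreement between arms is not always common. But at 0.8 SD the XOS-group test is almost always significant with no effect present. Complaints about the normality pre-test, or a demand for mixed models for quality of life, would be preferences and are not part of this point.

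None of this rescues the sentence on the paired test. It is a stated rule, and a fuller analysis plan could not make it correct.

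**Conclusion.** Wrong as written for the paired-test rule. If the within-group test is read as the article words it, an inert supplement would appear effective in 30% to 97% of trials for a common change of 0.3 to 0.8 SD with 25 per group. Those shifts are assumptions; the direction of the error is not, because both arms have chemotherapy in the window.

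The location gap is real but narrow. The Abstract and Introduction raise the XOS effect by tumour site as a question, no listed test addresses it, and separate tests would disagree 48% of the time under an equal 0.5 SD effect.

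Adjustment for stratum and week-3 value is a free improvement, worth 0.04 to 0.23 in power in the example above (0.74 − 0.70 to 0.93 − 0.70).

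**What to change.** In Data analysis:

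1. State that the between-arm comparison is the only test of the XOS effect. For continuous outcomes with a week-3 value, use ANCOVA of the week-15 value on treatment, tumour location and the week-3 value.
2. For capecitabine concentration, which has no baseline, adjust for location only.
3. Keep paired results as description, without calling them an assessment of the intervention.
4. Add the treatment-by-location term, reported as an estimate with its confidence interval, and state that no location difference will be inferred from separate p values.
5. Say plainly that this estimate will be imprecise, since 80% power needs a difference in effects of about 1.13 SD with 25 per cell.

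The cost is a change of wording and a little more analysis work in SPSS. No new data, visits or patients are needed.
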